### Blinding

Blinding participants to the TEPNS or TDES intervention is not feasible, as most individuals can perceive the electrical stimulation, and visible muscle contractions are required to confirm proper electrode placement. However, ultrasound images will be analyzed by a researcher who is blinded to the intervention procedure and image acquisition. Additionally, all file names will be coded and will not indicate the group to which the participant was allocated.

### Intervention

The intervention will be conducted in two different times, depending on the randomization sequence, and may begin with either TEPNS or TDES. A 1-hour washout period will be conducted between the two interventions. During interventions, participants will be instructed to breathe normally at tidal volume, using the perception of the electrical current as a cue for the onset of inspiration. This ensures synchrony with the stimulation cycle (“on” and “off” times), without altering the participant’s natural respiratory rhythm or pattern. For both the TEPNS and TDES, electrical stimulation will be applied continuously for 10 minutes in a single session.

### Transcutaneous electrical phrenic nerve stimulation (TEPNS)

The TEPNS parameters will be biphasic waves with a frequency of 10 Hz, a pulse width 200 μs, a rise time of 1.0 second, “on” and “fall” times of 1.0 second each, and a 2-second “off” time, resulting in 12 stimuli per minute [19]. TEPNS application will begin by identifying the right cervical phrenic nerve pathway using ultrasound, guided by anatomical landmarks including the anterior scalene muscle, sternocleidomastoid, internal jugular vein, and brachial plexus roots. The phrenic nerve appears as a hypoechoic (darker on ultrasound image), oval structure superficial to the anterior scalene muscle [20]. The active electrode (negative pole) will be placed along the nerve pathway between the heads of the sternocleidomastoid muscle using a 2 mm spherical microcurrent electrode (Neurodyn Esthetic, IBRAMED) (**Fig 3A and 3B**). The passive electrode (positive pole) will be positioned at the acromion shoulder to complete the electrical circuit [21] (**Fig 3C**). Stimulation intensity will be adjusted to the maximum level tolerated by the participant, sufficient to produce a diaphragmatic contraction confirmed by the ultrasound assessment without inducing contraction of the cervical or shoulder muscles [21].

**Fig 3 pone.0347493.g003:**
[figure not shown]
Electrostimulation technique: (A) 2 mm microcurrent stick, (B) microcurrent stick with connected spherical tip, (C) transcutaneous electrical phrenic nerve stimulation (TEPNS), and (D) transcutaneous diaphragmatic electrical stimulation (TDES).

### Transcutaneous diaphragmatic electrical stimulation (TDES)

The electrical parameters for TDES consist of biphasic waveform with a stimulation frequency of 30 Hz, a pulse width of 400 μs, a rise time of 1.0 second, an “on” time of 1.0 second, a fall time of 1.0 second, and an “off” time of 2 seconds, resulting in 12 stimuli per minute [19]. For TDES application, two self-adhesive electrodes (5.0 x 5.0 cm) will be placed bilaterally in the parasternal region, positioned inferior and lateral to the xiphoid process. An additional pair of electrodes will be placed bilaterally in the intercostal space between the 6th and 7th ribs, along the midaxillary line (**Fig 3D**). Electrode positioning will be guided by an initial ultrasound evaluation to identify the region of greatest visible diaphragmatic apposition. The stimulation intensity, measured in milliamperes (mA), will be gradually increased to the maximum level tolerated by the participant, until visible diaphragmatic contraction is achieved without concomitant contraction of abdominal muscles.

### Outcome measures

#### Diaphragmatic ultrasonography.

Diaphragmatic assessments will be performed using a LOGIQ E^®^ (R7) ultrasound system equipped with linear (GE12L-RS, 13 MHz) or a convex transducer (C1-5-D), in conjunction with water-based gel. Participants will be evaluated in supine position with a 30 degrees trunk inclination. Diaphragmatic mobility, thickness, and thickening fraction will be assessed. To measure tidal volume during the intervention, a facial mask will be connected to a ventilometer and a HEPA-filtered. The facial mask will be placed by the evaluator one minute before the assessment, and during two specific intervals: between the 4th and 5th and between the 9th and 10th minute of the intervention. Ultrasound evaluations will be conducted during spontaneous ventilation at tidal volume during both intervals, according to the randomization protocol.

Measurements of diaphragm mobility, thickness, and thickening fraction will be averaged from multiple respiratory cycles within the following three time points: (i) baseline (pre-intervention), (ii) 4–5 minutes into the intervention, and (iii) 9–10 minutes post-intervention. All ultrasound images will be exported to a secure storage device designated for research purposes only, with access restricted to authorized study personnel and researchers. While blinding is not feasible during image acquisition, a blind evaluator–who is not involved in the intervention or image collection–will perform the image analysis.

Diaphragmatic mobility will be assessed using a convex transducer (2–6 MHz) positioned in the right subcostal region along the mid-clavicular line, angled cephalically (**Fig 4A****-****4C**). Initially, B-mode ultrasound will be used to locate the diaphragmatic hemi-cupola. Once identified, M-mode will be employed to measure respiratory excursions, using the inferior vena cava and gallbladder anatomical landmarks. Mobility will be quantified as the vertical distance between the baseline position during expiration and the point of maximal diaphragmatic displacement during inspiration [22,23].

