#### Sensory discomfort evaluation.

Sensory discomfort will be assessed using a horizontal numeric discomfort rating scale. The scale will be presented in printed form on standard 10.0 cm paper, where “0” indicates no discomfort and “10” represents the worst imaginable discomfort. Participants will be asked to rate their perceived sensory discomfort for both interventions (i.e., TEPNS and TDES) at three time points: (i) Baseline – before the start of the intervention; (ii) Measure 5 – the first re-evaluation, conducted between the 4th and 5th minute of the intervention; and (iii) Measure 10 – the final re-evaluation, conducted during the last minute of the intervention [27].

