## Discussion

To our knowledge, this will be one of the first trials to directly compare two noninvasive electrical stimulation techniques applied to the diaphragm, TEPNS and TDES. Additionally, the randomized, single-blind, crossover design enhances internal validity while the bicentric conduction increases methodology rigor. Another strength of the present study protocol is the use of ultrasound to assess diaphragm thickness, thickening fraction and mobility, which provides an objective measure of diaphragm muscle recruitment and function.

Previous clinical investigations by Medrinal et al. [29] and Keogh et al. [30] reported no intervention-related adverse events associated with the use of non-invasive stimulation techniques applied to the diaphragm, supporting the safety of these approaches. In addition, no previous investigations have evaluated key ultrasound-derived parameters of diaphragmatic function such as diaphragm mobility, muscle thickness and thickening fraction as primary outcomes following stimulation interventions. The absence of prior data on these mechanistic endpoints precluded reliable assumptions regarding the expected effect size and consequently made an accurate a priori sample size calculation unfeasible. Therefore, an initial pilot phase including 12 participants was planned to provide preliminary estimates of variability and treatment effect. These data will be used to inform the sample size calculation for the main confirmatory crossover study described in this protocol.

The 1-hour washout period between stimulation conditions was defined to minimize the risk of potential carry-over effects in this crossover design. This interval was based on previous physiological and clinical studies on transcutaneous diaphragmatic electrical stimulation, suggesting that its effects on respiratory muscle activation, ventilatory parameters, and hemodynamic responses are predominantly acute and transient, with values returning to the baseline shortly after stimulation cessation [31].

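### The third ultrasound reading has two incompatible times: the last minute of stimulation, and 9–10 minutes after stimulation ends

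*Protocol article*

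**What the plan says.** All references are to the protocol article.

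- **Intervention.** For both techniques, "electrical stimulation will be applied continuously for 10 minutes in a single session".
- **Diaphragmatic ultrasonography, first paragraph.** The mask for measuring tidal volume is used in two windows, "between the 4th and 5th and between the 9th and 10th minute of the intervention". The ultrasound is tied to the same windows: "Ultrasound evaluations will be conducted during spontaneous ventilation at tidal volume during both intervals".
- **Diaphragmatic ultrasonography, second paragraph.** Mobility, thickness and thickening fraction are averaged over breaths at three time points. The first is a pre-intervention baseline, the second is "ii) 4–5 minutes into the intervention", and the third is "iii) 9–10 minutes post-intervention".
- **Sensory discomfort evaluation.** The third discomfort rating is "the final re-evaluation, conducted during the last minute of the intervention".
- **Discussion, washout rationale.** The effects of transcutaneous diaphragmatic stimulation (TDES) are described as acute and transient, "with values returning to the baseline shortly after stimulation cessation".
- **Sample size.** Diaphragm thickness is the sizing outcome. A 12-participant pilot will supply the within-participant difference and its SD. No time point is named here, nor in the mixed model under Statistical analysis.

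**The concern.** The two paragraphs describe different measurements. A reading in the last minute of a 10-minute session shows the diaphragm under current. A reading 9–10 minutes after the session shows whatever persists once the current is off. One third reading cannot be both.

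The conflict matters for three reasons. The list containing the off-stimulation time defines the data points for all three ultrasound outcomes, including the one used for sizing. The pilot difference and SD depend on which reading is taken. The planned correlations between ultrasound measures and discomfort would pair a current-off image with a current-on rating if the list were followed.

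**Working it through.** **1. Place both times on one clock.** Stimulation runs from minute 0 to minute 10 (Intervention).

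- First paragraph: minute 9 to 10 of the session, current on.
- List, item (iii): 10 + 9 = 19 to 10 + 10 = 20, so minute 19–20 from the start, current off.

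The two are about 10 minutes apart and lie on opposite sides of the end of stimulation. The list itself contrasts *into* for item (ii) with *post-* for item (iii), so its plain reading is after the session.

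**2. Compare with the rest of the document.**

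| Source | Minute 9–10, current on | Minute 19–20, current off |
|---|---|---|
| Ultrasonography, first paragraph (mask and ultrasound windows) | fits | does not fit |
| Discomfort schedule, final rating | fits | does not fit |
| Discussion, reason for a 10-minute session (acute activation) | fits | does not fit |
| Ultrasonography, list item (iii) | does not fit | fits |

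No other section describes a procedure at minute 19–20.

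**3. What the protocol says about persistence.** The washout rationale suggests a reduced response after stimulation stops. It concerns TDES studies and refers to muscle activation, ventilatory and hemodynamic responses. It does not mention phrenic nerve stimulation (TEPNS) or ultrasound thickness, and it gives no number of minutes. It supports a direction, not a size.

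**4. Illustration of what a reduced response would cost.** The protocol states no effect size, SD or final n, so there is no figure of its own to reproduce. From the Sample size section: paired t-test, two-sided α = 0.05, power 80%, dropout about 20%. Assumed here: a standardized paired difference d of 0.5 or 0.8 under current, a remaining fraction f of that difference at the reading, and an unchanged SD.

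- Power = P(|T| > t(0.975, n − 1)), where T is noncentral t with n − 1 degrees of freedom and noncentrality f·d·√n.
- Required n is the smallest n with power of at least 80%. Enrolled number = n / (1 − 0.20), rounded up.
- Approximate inflation of n = 1/f².

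| d | f | 1/f² | n | n with dropout | Power at the n for f = 1 |
|---|---|---|---|---|---|
| 0.5 | 1 | 1 | 34 | 43 | 81% |
| 0.5 | 0.75 | 1.78 | 58 | 73 | 57% |
| 0.5 | 0.50 | 4 | 128 | 160 | 29% |
| 0.5 | 0.25 | 16 | 505 | 632 | 11% |
| 0.8 | 1 | 1 | 15 | 19 | 82% |
| 0.8 | 0.75 | 1.78 | 24 | 30 | 58% |
| 0.8 | 0.50 | 4 | 52 | 65 | 30% |
| 0.8 | 0.25 | 16 | 199 | 249 | 11% |

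The table applies only if the off-stimulation reading carries the comparison and the trial was sized on the on-stimulation difference. If the pilot and the main trial both used the off-stimulation reading, the pilot estimates would already reflect it. The trial would then be answering a different question rather than being sized on the wrong difference.

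**The case against.** The best defence is that this is a single wrong word. The numerals 9–10 match the on-stimulation window exactly, the discomfort schedule has the same three-point structure, and the Discussion speaks of acute activation and plans no recovery reading. The article also condenses a fuller protocol, and its schedule and flow figures, which could not be consulted, may show the timing. Most of this stands, and it is why the on-stimulation time is the likely intent. It does not remove the conflict: the odd wording is in the list that defines the time points, and no sentence in the article overrides it.

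Three stronger readings are tempting but unsupported.

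- *The primary outcome would be read after the effect has gone.* The washout statement is limited to TDES, does not name thickness and puts no minutes on the return to baseline. No primary time point is named, and the 4–5 minute reading is under current in both paragraphs.
- *The contrast would halve and the sample size would rise fourfold.* That is the row f = 0.50, an assumed value. The protocol gives neither a remaining fraction nor a share of readings taken off-stimulation, and it has no fixed n to inflate.
- *The two sites are mixing two outcomes.* Nothing shows that they follow different sentences. A timestamp check is a sensible precaution, not a response to known divergence.

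**Conclusion.** The point holds as an internal contradiction about when the third reading of thickness, thickening fraction and mobility is taken. The wording after the intervention is probably a slip. If it were followed, the third reading would show residual rather than on-stimulation response and would be out of step with tidal volume and discomfort.

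The firm size of the discrepancy is about 10 minutes, with current on in one case and off in the other. Any loss of power depends on an unknown remaining fraction f and on how much weight the third reading carries. Across the assumed f of 0.75 to 0.25, the required n rises by about 1.8 to 16 times. If no difference remained, no n would suffice. The matter needs settling before the pilot difference and SD are used for sizing.

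**What to change.** Change item (iii) of the time-point list to 9–10 minutes into the intervention, so that it agrees with the paragraph before it and with the discomfort schedule. The sponsor should confirm that this is the intent.

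Recruitment began in April 2024, so images may already exist. Check their acquisition times at both sites against the end of stimulation, and flag any third reading taken after current-off. Do this before the pilot estimates are calculated.

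The cost is one corrected sentence and a timestamp check. No new procedure is needed.

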**Fig 4 pone.0347493.g004:**
[figure not shown]
Technique for ultrasound evaluation of diaphragmatic muscle thickness: **A)** Convex transducer. **B)** Cake-shaped image on the screen in “brightness – B” mode. **C)** Mobility assessment in “motion – M” mode. Convex transducers are primarily used for abdominal exams due to their wider and deeper view. **D)** Linear transducer. **E)** Cake-shaped image on the screen in “brightness – B” mode. **F)** Mobility assessment in “motion – M” mode.

Diaphragmatic thickness (Tdi) and thickening fraction will be assessed using a high-frequency linear transducer (7–13 MHz) placed over the diaphragm's zone of apposition (ZA) (**Fig 4D****-****4F**). This zone is located between the 8th and 9th intercostal spaces, approximately 0.5 to 2.0 cm below the costophrenic angle (**Fig 4F**) [24,25]. The diaphragm will be identified as a hypoechoic muscle layer bordered by hyperechoic pleural and peritoneal membranes [26]. “Tdi” will be measured as a distance between the pleural and peritoneal lines at the end of expiration (Tdi-exp) and at the end of inspiration (Tdi-insp). The diaphragmatic thickening fraction will be calculated as the percentage increase in thickness from inspiration to expiration, using the following formula: [F_Ei_ = (E_i_ – E_e_ / E_e_) x 100]. Where “FEi” is the inspiratory muscle thickening fraction; “Ei” is the muscle thickness at the end of inspiration; and “Ee” is the muscle thickness at the end of expiration [23].

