Noninvasive stimulation of diaphragm contraction has been investigated, however, the heterogeneity of protocols and NMES parameters used—combined with the anatomical complexity of locating the diaphragm’s motor point—limits the reproducibility and clinical applicability of this technique [15–17]. Therefore, the primary objective of this study is to compare the effects of TEPNS and TDES on diaphragm thickness, thickening fraction, and diaphragmatic mobility in healthy adults.

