### Sample size

Since no previous studies have evaluated the effects of this specific intervention on the diaphragm thickness, an initial pilot phase including 12 participants will be conducted to obtain preliminary estimates of variability and treatment effect. These data will be used to inform a formal sample size calculation for the main crossover trial. The primary outcome for sample size determination will be diaphragm thickness. The sample size calculation will be based on the expected within-participant mean difference between intervention conditions and the corresponding standard deviation derived from the pilot data, assuming a paired t-test framework. The required sample size will be estimated considering a two-sided significance level of 5% (α = 0.05) and a statistical power of 80%. Additionally, a potential dropout rate of approximately 20% will be incorporated to ensure adequate statistical power for the final analysis.

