### Statistical analysis

The Research Electronic Data Capture (REDCap) platform will be used for data entry and storage. Continuous variables will be reported as mean ± standard deviation (SD) for normally distributed data, or as median and interquartile range (IQR, 25th–75th percentile) for non-normally distributed data. Categorical variables will be presented as absolute numbers and percentages. Normality will be assessed using the Shapiro–Wilk test. For within-participant comparisons between TEPNS and TDES conditions, paired t-tests will be used for normally distributed data, and the Wilcoxon signed-rank test will be applied for non-parametric data. The primary analysis will be performed using a linear mixed-effects model appropriate for a two-period crossover design, including treatment, period, and sequence as fixed effects, and participant as a random effect, thereby accounting for within-subject correlation. Percentage changes in diaphragm thickness, thickening fraction, and mobility will also be calculated.

The frequency of adverse events will be systematically recorded and descriptively analyzed to characterize the safety profile of both interventions. Additionally, associations between diaphragm thickness, thickening fraction, diaphragmatic mobility, stimulation intensity, participant-reported discomfort, and the occurrence of adverse events will be explored using Pearson’s or Spearman’s correlation coefficients, as appropriate. Adjustment for multiple comparisons will be performed where applicable to control the risk of type I error. Missing data will be addressed using multiple imputation by chained equations under the missing-at-random assumption. Each imputed dataset will be analyzed separately, and the results will be pooled using Rubin’s rules to obtain valid statistical inferences.

All statistical analyses will be performed using the Statistical Package for the Social Sciences (SPSS) version 28.0.1 (SPSS Inc., Chicago, IL, USA). A two-sided p-value < 0.05 will be considered statistically significant. The statistician responsible for data analysis will be blinded to the allocation sequence and intervention timing.

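### The article's only definition of diaphragmatic thickening fraction is misprinted twice: the formula lacks the bracket around its numerator, and the wording reverses the direction

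*Protocol article*

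**What the plan says.** The definition stands in the protocol article, Methods, Outcome measures, Diaphragmatic ultrasonography, in the paragraph after the Fig 4 caption. Thickness is measured at end-expiration (Tdi-exp) and at end-inspiration (Tdi-insp). The thickening fraction is then described as the "percentage increase in thickness from inspiration to expiration" and given by "F_Ei_ = (E_i_ – E_e_ / E_e_) x 100" (the underscores mark subscripts). The symbols are explained next: "Ei” is the muscle thickness at the end of inspiration" and "Ee” is the muscle thickness at the end of expiration". FEi itself is called the inspiratory muscle thickening fraction.

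Three other places show how the outcome is used:
- The Introduction states the primary objective as to "compare the effects of TEPNS and TDES on diaphragm thickness, thickening fraction, and diaphragmatic mobility in healthy adults".
- The Sample size section rests on a different measure: "The primary outcome for sample size determination will be diaphragm thickness".
- The Statistical analysis section adds that "Percentage changes in diaphragm thickness, thickening fraction, and mobility will also be calculated", and lists thickening fraction among the variables for exploratory correlations.

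**The concern.** This is a calculation rule stated in the Methods, not a detail left to another document, and it is the only definition of this outcome in the article. The formula and the sentence that introduces it disagree with each other, and neither states the usual relative increase.

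A thickening fraction is meant to express contraction relative to the resting (end-expiratory) thickness. Followed literally, the formula loses that reference, and the outcome becomes end-inspiratory thickness shifted by 1 and multiplied by 100. The difference between the two conditions would then be 100 × (Ei under TEPNS − Ei under TDES). A paired t-test on it would be the same test as one on end-inspiratory thickness, so the outcome would carry no information of its own. The percentage change in it would become (Ei2 − Ei1)/(Ei1 − 1), where Ei1 and Ei2 are the values at the earlier and later time points. That ratio depends on the unit and is unstable when Ei1 is near 1.

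**Working it through.** **Inputs.** The formula, the verbal direction and the definitions of Ei and Ee come from the Diaphragmatic ultrasonography section. The article gives no thickness values, so those below are assumptions chosen only to show how each expression behaves. The article has no stated figure to reproduce.

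**Step 1: the formula as printed.** Division comes before subtraction, so

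(Ei − Ee/Ee) × 100 = (Ei − 1) × 100.

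Ee has cancelled.

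**Step 2: the intended form.** With the numerator bracketed: [(Ei − Ee)/Ee] × 100.

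**Step 3: the wording read literally.** A relative change from inspiration to expiration is [(Ee − Ei)/Ei] × 100. It is negative whenever Ei exceeds Ee, so it cannot be an increase in a muscle that thickens on inspiration.

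**Step 4: numbers.**

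| Ei, Ee (assumed) | As printed | Bracketed | Wording taken literally |
|---|---|---|---|
| 2.4, 2.0 mm | (2.4 − 1) × 100 = 140 | 0.4/2.0 = 20% | −0.4/2.4 = −16.7% |
| 2.4, 1.6 mm | (2.4 − 1) × 100 = 140 | 0.8/1.6 = 50% | −0.8/2.4 = −33.3% |
| 2.4, 1.2 mm | (2.4 − 1) × 100 = 140 | 1.2/1.2 = 100% | −1.2/2.4 = −50% |
| 0.24, 0.16 cm | (0.24 − 1) × 100 = −76 | 0.08/0.16 = 50% | −0.08/0.24 = −33.3% |

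The first three rows share one Ei, and the printed formula cannot tell them apart although the bracketed index runs from 20% to 100%. The second and fourth rows are the same muscle in two units: the printed formula moves from 140 to −76, while the bracketed index stays at 50%.

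**Step 5: can one half repair the other?** The wording gives the wrong direction and the wrong denominator, so it cannot be used to restore the missing bracket. The symbol definitions and the name of the measure can: both thicknesses are defined, Ee is subtracted from Ei, and Ee is the divisor.

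**The case against.** The strongest reply is that no competent reader would compute Ei − 1. The paragraph calls the quantity a fraction and a percentage increase, and it defines Ee, which would serve no purpose in the formula if it cancelled. Only (Ei − Ee)/Ee fits all of that, so this is a missing bracket and two transposed words, not a different outcome. That stands, and it limits the severity.

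A typesetting or text-conversion cause for the missing bracket also cannot be fully excluded. However, the slash and the outer parentheses survived in line, and no such cause explains the reversed wording, which is plain prose.

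A reader might go further and infer that a calculated field in the data-capture system, or a script at one of the two sites, will carry the error into the results. The document does not support this. REDCap is described only for data entry and storage, no calculated field or script is mentioned, and image analysis is assigned to a blinded evaluator rather than to separate site teams. If a wrong value were produced, the loss would be recoverable: both thicknesses are measured and the images are exported and stored. Some errors would also show themselves, such as a negative fraction from thicknesses in centimetres.

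What remains after all this is that the one stated rule gives a wrong answer if followed.

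**Conclusion.** The point holds as an error in a stated definition. The printed formula equals (Ei − 1) × 100 exactly, whatever the data, and the wording contradicts the formula's own order of subtraction. Because the article offers no other definition and the outcome belongs to the primary objective, it should be corrected.

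Its reach is limited. The gap between 140 and 20% or 50% rests on assumed thicknesses and shows how the expression behaves; it does not estimate an error in this trial. It would be wrong to conclude that the trial's thickening-fraction results are or will be invalid, since the intended index can be inferred and nothing shows how it is actually being computed. It would be equally wrong to extend the point to the sample size, which is to be calculated from diaphragm thickness, or to thickness and mobility, which are measured directly and do not use this formula.

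**What to change.** Replace the formula with TF = [(Ei − Ee) / Ee] × 100 and describe it as the percentage increase in thickness from end-expiration to end-inspiration. Keep the symbol definitions as they are. Confirm that the analysis computes the outcome this way, and keep both thicknesses in the dataset so that the fraction can be rederived.

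The cost is one sentence and one formula, plus a brief check of the calculation. No change to design, measurement or data collection follows. The article reports that recruitment is under way and that no results exist yet, so the correction can be made before any analysis.
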